## Abstract

**Background:**

Gluteal tendinopathy (GT) is a degenerative tendon condition characterised by pain over the greater trochanter of the hip. A randomised controlled trial (RCT) in Australia found that 14 sessions of EDucation on load management plus eXercise (EDX) delivered over 8 weeks resulted in greater improvements in global rating of change and pain outcomes at 8 and 52 weeks, compared with corticosteroid injection or ‘wait and see’. Typically, 5-6 physiotherapy sessions are provided in public and private physiotherapy settings in Ireland, therefore, the aim of this study is to examine the feasibility of conducting a future definitive RCT to investigate effectiveness of 6 sessions of the EDX programme compared to usual care.

**Methods:**

We will randomly allocate 64 participants with GT to physiotherapist-administered EDX or usual care. The EDX intervention (EDX-Ireland) will be delivered in 6 sessions over 8 weeks.

To determine feasibility of an RCT, we will assess recruitment and retention and outcome measure completion. The health status outcomes to be assessed at baseline, 8 weeks and 3 months include: Global Rating of Change, pain severity, the Victorian Institute of Sport Assessment-Gluteal Questionnaire (VISA-G), the Patient-Specific Functional Scale, the Pain Catastrophizing Scale, Patient Health Questionnaire (PHQ), Pain Self-Efficacy Questionnaire, the EQ-5D-5L, the Central Sensitisation Inventory and hip abductor muscle strength. We will explore acceptability of the EDX-Ireland intervention from the perspective of patients and treatment providers, and the perspective of referrers to the trial. A Study Within A Trial will be also applied to compare recording of exercise adherence using app-based technology to paper diaries.

**Discussion:**

There is a need to establish effective treatments for GT that potentially can be implemented into existing health systems. The findings of this feasibility trial will inform development of a future definitive RCT.

**Registration:**

The trial is registered prospectively on ClinicalTrials.gov (
NCT05516563, 27/10/2022).

## Background 

Gluteal Tendinopathy (GT) is a degenerative condition of the gluteus medius and minimus tendons characterised by lateral hip pain at or around the greater trochanter of the hip, with marked palpation tenderness (
Fearon *et al.*, 2014). It is also known as Greater Trochanteric Pain Syndrome (GTPS). GTPS is an umbrella term used to describe pain over the greater trochanter of the lateral hip, primarily due to gluteus medius and/or minimus tendinopathy, with symptoms also potentially arising from the trochanteric bursa (
Long *et al.*, 2013). However, the terminology of gluteal tendinopathy is used when gluteus medius and/or minimus tendon changes are detected on Ultrasound (US) or Magnetic Resonance Imaging (MRI) (
Bird *et al.*, 2001;
Connell *et al.*, 2003). Trochanteric bursitis has been shown to be present in less than 20% of those with lateral hip pain (
Long *et al.*, 2013).

GT is the most common lower limb tendinopathy with a reported prevalence of 4.22 per 1000 person years and incidence of 3.29 per 1000 person years, and is three times more prevalent in women than men, (
Albers *et al.*, 2016;
Segal *et al.*, 2007). GT can result in very high levels of hip dysfunction, with consequent negative impact on general health and well-being, quality of life and employment status, similar to end-stage hip osteoarthritis (
Fearon *et al.*, 2014;
Plinsinga *et al.*, 2018).

Along with structural changes in the gluteus medius and minimus tendons (
Connell *et al.*, 2003), individuals with GT have reduced hip abductor strength (
Allison *et al*., 2016b) and higher external hip adduction moments during loading activities such as walking and stair-climbing (
Allison *et al.*, 2018;
Allison *et al*., 2016a).

Abnormal hip biomechanics may predispose the development of GT. Specifically, it has been hypothesised that gluteal tendinopathy occurs due to compressive impingement of the gluteal tendons and bursa onto the greater trochanter by the iliotibial band (ITB) as the hip moves into adduction. Compressive forces are increased due to potential hip abductor muscle weakness, resulting in lateral pelvic tilt or ipsilateral shift in single leg stance, and relative hip adduction (
Grimaldi & Fearon, 2015).

Although this evidence highlights the rationale for strengthening as a key intervention, traditionally, corticosteroid injections have been used to achieve pain relief. The lack of evidence for the long-term benefits of steroid injection (
Mellor *et al.*, 2018;
Nissen *et al.*, 2019;
Rompe *et al.*, 2009) highlights that interventions that result in long-term benefits are required. Additionally, steroid injections can, make tendons more vulnerable to tears (
Abate *et al.*, 2017).

There is general consensus, in line with management of other tendinopathies, that interventions should aim to reduce compressive and tensile loads through education on how to minimise or adapt compressive activities and positions such as single-leg stance (walking, running and stair climbing), adduction-related activities such as sitting with legs crossed, certain hip stretches and sleeping positions (
Grimaldi & Fearon, 2015).

Although a range of conservative management approaches are generally recommended, best practice in the management of GTPS/gluteal tendinopathy remains unclear. A three-arm Randomised Controlled Trial (RCT) in Australia (LEAP trial) compared 14 sessions of EDucation on load management plus eXercise (EDX) over 8 weeks to a single corticosteroid injection (CSI), and a ‘wait and see’ comparison group on pain and global improvement in 204 individuals with GT. Results showed that at 8 weeks (completion of treatment), 77% of the EDX group were at least ‘moderately better’, compared with 58% in the injection group, and 29% in the ‘wait and see’ group, with improvements maintained at one year and less pain was reported by the EDX group than the corticosteroid injection and ‘wait and see’ groups. Additionally, at 8 weeks a significant difference in hip abductor strength was found between the EDX and the ‘wait and see' group (
Mellor *et al.*, 2018).

However, the 14 physiotherapy treatment sessions provided in the LEAP Trial (
Mellor *et al.*, 2018) may not be feasible in physiotherapy practice. For example, although exercise and education are the most common interventions for GT delivered by physiotherapists in Ireland, the number of physiotherapy sessions is usually limited to five or six (
[name] *et al.*, 2019). This treatment dosage is consistent across various musculoskeletal pathologies in the UK (
Bury & Littlewood, 2018). Thus, whilst the LEAP trial in Australia demonstrated positive effects for EDX, delivery of this intervention over 14 sessions may not be practical to implement into physiotherapy practice, and evaluation of a lower dose of face-to-face sessions with a healthcare practitioner, which could be implemented into clinical practice is warranted.

Although current best evidence indicates, based on the LEAP trial findings, that a combination of physiotherapist-delivered exercise and education is clinically and cost-effective for management of GT (
Mellor *et al.*, 2018;
Wilson *et al.*, 2023), there are currently no clinical guidelines to guide practice. Indeed, usual care of gluteal tendinopathy by medical practitioners, to whom patients may initially present, is currently unknown.

This feasibility RCT will contribute to the following gaps in the literature: 1) to examine the feasibility of conducting a future definitive RCT to compare effectiveness of six sessions of physiotherapy-led Education on load management plus eXercise (EDX-Ireland) EDX to usual care and 2) to quantify usual care in GT management in Ireland.

Completion of a daily Home Exercise Programme (HEP) is an integral part of the EDX-Ireland intervention. Traditionally, paper-based diaries are used to record adherence, but adherence can be over-reported compared with electronic diaries (
Stone *et al.,* 2003). An RCT demonstrated improved exercise adherence using an app in people with musculoskeletal conditions, compared to paper handouts (
Lambert *et al.*, 2017), with high satisfaction rates reported by those who used the app. Given that >90% of phone users in Ireland have smartphones (
Deloitte, 2023), the use of app-based technology may be potentially more feasible to monitor and enhance treatment adherence.

We therefore aim to evaluate the feasibility of conducting a future definitive RCT, using a reduced dose (6 sessions) of a proven-effective physiotherapy treatment (14 sessions) consisting of EDucation plus eXercise for GT in an Irish context. A Study Within A Trial (SWAT) will compare smartphone application
*versus* paper-based diary for exercise adherence measurement. A SWAT is a type of research study that has been embedded within a host larger trial to evaluate alternative ways of delivering or organising a particular trial process (
Treweek *et al.*, 2018).

### Objectives

Specific objectives are as follows:

1. To assess recruitment and retention rates to inform a future definitive RCT

2. To estimate the effect size for an appropriate primary study outcome in a future definitive RCT

3. To determine the success of different patient recruitment methods (community recruitment, primary care and secondary care)

4. To identify the constituents of 'usual care' for gluteal tendinopathy in an Irish context and to determine if inclusion of a usual care arm in a future definitive RCT is feasible and appropriate without the potential for co-intervention bias

5. To assess outcome measure completion

6. To assess the feasibility of collecting healthcare utilisation and cost data for cost-effectiveness analysis

7. To assess if adherence to the home exercise programme (HEP) for those allocated to the EDX-Ireland intervention differs when recorded
*via* a smartphone application compared with paper diaries

8. To assess the acceptability of the EDX-Ireland intervention and usual care from the perspective of study participants and service providers (treating therapists and providers of usual care)

9. To assess participants’ and therapists’ acceptability of a smartphone-based application (app) for exercise provision and home exercise adherence recording in the EDX-Ireland arm

10. To compare EDX with usual care on clinical outcomes including pain, function, hip abductor muscle strength, psychological measures, and quality of life.

## Methods

### Design and study setting

This feasibility, assessor-blinded RCT will take place in Dublin, Ireland. Telephone and physical screening will take place at RCSI, while the EDX-Ireland intervention will be delivered in four physiotherapy clinics located in various northside and southside Dublin locations. The trial protocol follows the Standard Protocol Items: Recommendations for Interventional trials (SPIRIT) guidelines adapted for the reporting of protocol manuscripts of pilot and feasibility trials (
Chan *et al.*, 2013). An overview of the LEAP-Ireland procedure is outlined in
Figure 1. The model consent form can be found as
*Extended data* (
[name] & [name], 2023a). The trial is registered prospectively on ClinicalTrials.gov (
NCT05516563, 27/10/2022).

**Figure 1. f1:**
[figure not shown]
Overview of LEAP-Ireland procedures.

### Ethics approval

Ethics approval for this study has been granted by Research Ethics Committee of the Royal College of Surgeons in Ireland (RCSI) (REC202205010) on 19/08/2022, Irish College of General Practitioners (ICGP) (ICGP_REC_22_012) on 28/06/2022, Mater Misericordiae University Hospital (1/378/2303) on 25/10/2022, Beaumont Hospital (22/29) on 07/03/2023 and St Vincent's University Hospital (RC22-023) on 13/10/2022.

### Participants

As the EDX programme in this trial has been designed specifically to address gluteal tendinopathy, other differential diagnoses for lateral hip pain such as hip osteoarthritis are excluded (
Woodley *et al.*, 2008) thus, various eligibility criteria will be applied.

Table 1 outlines the inclusion and exclusion criteria, which are based on the LEAP trial (
Mellor *et al.*, 2018). 

**Table 1. T1:** Inclusion and exclusion criteria.

Inclusion Criteria	Exclusion Criteria
• Aged 35–70 years • Lateral hip pain for at least 3 months, of ≥ 4/10 on an 11- point NPRS on most days of the last 3 months • Tenderness on palpation of the greater trochanter • Reproduction of lateral hip pain on at least one of following diagnostic clinical tests: (FADER test, FADER with static muscle test (internal rotation) at end of range (FADER- R), FABER test, passive hip Adduction in side-lying (ADD) test, adduction with resisted isometric abduction (ADD-R), and single leg stand (SLS) for 30 seconds • Demonstrated tendon pathology on MRI	• Previous cortisone injection in the region of the lateral hip in the last 12 months • Physiotherapy (including regular Physiotherapy-led Pilates) for lateral hip pain in the last 3 months • Lumbar spine or lower limb surgery in the last 6 months • Any known advanced hip joint pathology where groin pain is the primary complaint and/or where groin pain is experienced at an average intensity of ≥2 on most days of the week, or Kellgren-Lawrence score of >2 (mild) on X-Ray • Clinical criteria for the diagnosis of hip osteoarthritis (Altman *et al.*, 1991) ○ Self-reported hip pain with either hip internal rotation <15° and hip flexion ≤115°, or ≥15° hip internal rotation and pain on hip internal rotation ○ Morning stiffness ≤ 60 minutes ○ Age ≥ 50 years ○ Hip joint flexion <90°, bilaterally • Lumbar radiculopathy or pain in another body location greater than the hip pain • Known advanced knee pathology or restricted knee range of motion (must have minimum 90° flexion and full extension, bilaterally) • Any systemic diseases affecting the muscular or nervous system, or uncontrolled diabetes • Fibromyalgia • Use of walking aid • Malignant tumour (current or in the past 6 months) • Systemic inflammatory disease • Any factors that preclude the participant from having an MRI (e.g., pacemaker, metal implants, pregnancy, or trying to become pregnant, claustrophobia) • If the participant is involved in any injury claim • If the participant is unable to commit to an 8-week programme of up to 6 sessions of exercise • If the participant is unable to write, read or comprehend English • Unable or unwilling to use technology for exercise prescription and adherence

FABER, Flexion, Abduction, External Rotation; FADER, Flexion, Adduction, External Rotation; MRI, Magnetic Resonance Imaging; NPRS, Numerical Pain Rating Scale.

### Recruitment

Participants will be recruited from various sources, including rheumatology, orthopaedic and musculoskeletal triage clinics in three acute hospitals in Dublin, General Practitioners (GPs), social media and community recruitment throughout Dublin
*via* advertisements in sports and leisure clubs and community organisations.

### Procedure

Eligibility will be assessed through a 3-phase process of phone screening, physical screening and MRI. Initial screening for eligibility will be done
*via* telephone by the Trial Manager (SA). If the phone interview indicates possible eligibility, potential participants will attend RCSI for a physical examination against specific selection criteria, undertaken by the Trial Manager. A battery of clinical tests will be used at the physical screening stage to clinically diagnose GT (
Grimaldi *et al.*, 2017). To be eligible, participants must experience pain on direct palpation of the gluteal tendon insertion on the greater trochanter, with reproduction of lateral hip pain on at least one of the following clinical tests: Hip Flexion, Adduction, External Rotation (FADER), resisted internal rotation in the FADER position (FADER-R), Flexion, Abduction, External Rotation (FABER), passive hip adduction in side lying (ADD), resisted isometric abduction in the ADD test position ADD-R), and a Single Leg Stance on the affected leg for 30 seconds (
Mellor *et al.*, 2016). If participants meet the physical screening eligibility criteria, an MRI will be arranged to confirm the tendinopathic changes on MRI. Criteria for tendon pathology on MRI as used by
Mellor *et al.* (2016) were adapted from
Blankenbaker *et al.* (2008) (
Table 2).

**Table 2. T2:** MRI classification of pathology for definition of gluteal tendinopathy (
Blankenbaker *et al.*, 2008).

T2 Hyperintensity around Greater Trochanter (representing oedema/fluid	
**Size**	(1) Tiny (thin slit of fluid) (2) Small (localized, mild distension) (3) Medium (localized, moderate distension) (4) Large (localized, marked distension)
**Shape**	(1) Feathery (2) Crescentic (3) Round (distended bursa)
**Location**	(1) Subtendinous (2) Intratendinous * (3) Subfascia lata (4) Superficial to fascia lata
**Partial thickness tear**	Tendon irregular, thinned or focally Discontinuous
**Full thickness tear**	Discontinuity and/or retraction of the torn tendon from greater trochanter

*Intratendinous high T2 signal considered as tendinopathy with a thickened tendon without any irregularity, tendon thinning, or focal tendon discontinuity. MRI, Magnetic Resonance Imaging.

Written consent will be obtained at the time of physical screening for pragmatic purposes, but full eligibility will be confirmed on the basis of the MRI results. Once participants complete the baseline assessment, they will be randomly allocated into one of two groups: (1) education and exercise programme (EDX-Ireland), or (2) usual care. Participants will complete the patient-reported outcomes (PROs) and abductor muscle strength assessment at baseline, 8 weeks, and 3 months.

Participants will be asked to refrain from other treatments during the trial period, but analgesia and anti-inflammatory drugs will be permitted. All medication use and co-interventions will be recorded
*via* the healthcare utilisation questionnaire.

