### Usual care

In the LEAP trial '’wait and see’’ arm, participants attended one 30-minute session with a trial physiotherapist, where they received reassurance that the condition is likely to resolve over time, as well as advice regarding general tendon care and self-management (
Mellor *et al.*, 2016). However, usual care in the LEAP-Ireland trial was chosen as the comparator for this study to determine if it is an appropriate comparator, and to identify the exact constituents of usual care, in advance of conducting a full-scale RCT. Usual care for this trial is defined as the treatment that a participant has followed so far or has been prescribed by their referrer into the trial (
*i.e.*, GP, orthopaedic consultant, rheumatologist or musculoskeletal triage physiotherapist). For those not referred from a healthcare practitioner (
*e.g.*, community recruitment/social media), usual care may not be relevant, but any healthcare utilisation will be recorded on a pre-standardised form. Participants randomised to the Usual Care group will receive an information leaflet only with general advice to remain active within limits of pain, and reassurance that the condition will improve with time. The information leaflet is identical to that used in the LEAP Trial, however, no one-off education physiotherapy session will be provided for the Usual Care group. 

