### Statistical analysis

Descriptive analysis will include proportions and 95% confidence intervals (CI), means and standard deviations (SD) or medians and inter-quartile ranges (IQR) where appropriate. Feasibility outcomes of recruitment and retention rates will be descriptively reported overall across both arms of the trial (percentages and 95% CIs) and by method of recruitment. Outcome measure completion will be described both by participant and by outcome measure using percentages. Recruitment rates will be calculated as the number of participants who consent to participate divided by the number of eligible participants approached. Trial retention rates will be calculated from the number of participants who complete all outcome measures divided by the number who record baseline outcome measures. Adherence rate of exercises within the SWAT for the EDX group, and types of usual care for the control group will be reported as percentages.

Results of secondary clinical outcomes including NPRS, hip abduction strength and measures of psychological distress will be reported using means and SD or medians and IQR, where appropriate for baseline, 8- and 3- month follow-up. Statistical analysis will be performed using Stata v18 (StataCorp, College Station, Texas, USA).

Sensitivity analysis will be conducted as a secondary analysis to impute any missing data using multiple imputation. The resource use data captured by the OCC-Q will be valued using unit costs derived from local and national sources and will be analysed in a manner consistent with the clinical outcome data.

Qualitative data from interviews will be transcribed verbatim. A two-stage analysis will be undertaken, initially through inductive line-by-line coding of the extracted results to identify emergent themes, followed by deductive mapping of pre-identified codes to the Theoretical Framework of Acceptability (
Sekhon *et al.*, 2017).

Trustworthiness will be attained through procedures such as member checking, maintaining a reflexive journal of the research procedures and a clear audit trail of the process (
Braun & Clarke, 2014).

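### The request to forgo other treatments conflicts with the definition of usual care, so care seen after randomisation may reflect the trial's own instruction

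*Protocol article*

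**What the plan says.** Four parts of the protocol article bear on what a control participant does and receives.

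- **Procedure.** Immediately after both arms are introduced: "Participants will be asked to refrain from other treatments during the trial period, but analgesia and anti-inflammatory drugs will be permitted". No exception is made for the usual care arm. The section adds that medication use and co-interventions are recorded through the healthcare utilisation questionnaire.
- **Usual care.** The definition reads: "Usual care for this trial is defined as the treatment that a participant has followed so far or has been prescribed by their referrer". Later in the same section: "Participants randomised to the Usual Care group will receive an information leaflet only with general advice to remain active within limits of pain". For people who come through community or social media recruitment, "usual care may not be relevant, but any healthcare utilisation will be recorded on a pre-standardised form".
- **Table 3 (feasibility outcomes).** Referrers complete a checklist of usual care options that covers medications and referral for physiotherapy or other services. It is checked against the participant's health and cost questionnaire. Participants also report current and past treatment at baseline.
- **Statistical analysis.** "types of usual care for the control group will be reported as percentages".

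Objective 4 is the aim that depends on these passages: "To identify the constituents of 'usual care' for gluteal tendinopathy in an Irish context and to determine if inclusion of a usual care arm". The objective goes on to ask whether such an arm would be workable and suitable, free of possible co-intervention bias. The Sample size section also intends the between-arm GROC effect to inform the powering of a definitive trial.

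**The concern.** In most trials a loosely described usual care arm is a reporting weakness. Here the comparator is itself under study. Quantifying usual care in Ireland is one of the two gaps that the Background says the trial will fill, and the Discussion expects the findings to guide the choice of comparator for the definitive trial.

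If control participants comply with the request in the Procedure section, they will show little non-drug care and little co-intervention during follow-up. That could be read as evidence that usual care is sparse and that a usual care arm is safe from contamination, when the trial had asked for exactly that. The GROC contrast would share the problem. Nobody could say whether it compares the EDX programme with care as normally delivered, or with a leaflet plus permitted drugs.

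**Working it through.** This is a question of wording, and no figure in the plan changes under it. The article's only precision figures do reproduce. With p ± 1.96 × √(p(1−p)/60), a 50% rate gives 37.35% to 62.65% (stated 37.3% to 62.7%) and an 80% rate gives 69.88% to 90.12% (stated 69.8% to 90.2%). They concern recruitment and retention and do not bear on this point.

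**Step 1: one case under each passage.** Take a control participant whose GP has referred them for physiotherapy at the time of entry.

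| Place | What follows for this participant |
|---|---|
| Procedure | Asked not to take up the physiotherapy; only analgesia and anti-inflammatory drugs are excepted |
| Usual care, definition | The physiotherapy is the control condition, because the referrer prescribed it |
| Usual care, leaflet sentence | The trial gives a leaflet; whether the physiotherapy may go ahead is not said |
| Table 3 | The referral is counted as a constituent of usual care |

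The first row conflicts with the second and fourth. The third does not settle the matter. Staff working from the Procedure section and staff working from the definition would run different control arms.

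**Step 2: a community recruit.** There is no referrer, so the definition can reach only treatment already followed, and the article says usual care may not be relevant. This is one of the three strata used for randomisation (GP, secondary care, community/social media). The content of the control arm therefore differs by stratum. The article does not say how many of the 64 participants will fall in it.

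**Step 3: which data sources depend on the request.**

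- Referrer checklist: records what was prescribed, so it does not depend on the request. I assume it is completed at or near referral; the article does not give its timing.
- Current and past treatment at baseline: collected before allocation, so independent of the request in either arm.
- Healthcare-use questionnaire to 3 months: depends on it directly, because it records what participants did after being asked to hold back.
- Interviews with about 8 to 10 referrers: record their rationale for usual care, so largely independent.

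The loss therefore falls on post-randomisation care and co-intervention. What was prescribed or used beforehand can still be described.

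**Step 4: who is in the sample.** Table 1 excludes "Previous cortisone injection in the region of the lateral hip in the last 12 months" and physiotherapy for lateral hip pain in the last 3 months. Older treatment remains eligible and is captured as past treatment, and a fresh referral for physiotherapy is not excluded. Recent users of these two treatments are nonetheless absent by design, so the profile describes usual care among people without recent use of either.

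**The case against.** The strongest reply is that each sentence has a harmless reading. The leaflet sentence probably describes what the trial itself supplies, since the next one contrasts it with the one-off physiotherapy session given in the LEAP trial's comparison arm; that can coexist with continuing referrer care. Other treatments may mean treatments outside the allocated arm, and participants are asked, not obliged. Variation in usual care is also acknowledged openly and is part of what the trial studies.

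Much of this stands. I accept the first reading of the leaflet sentence as likely, so a reader who infers three mutually incompatible comparators goes too far. The second reading is possible but unstated. The drug exception sits awkwardly with it, because Table 3 lists medications among usual care options and controls would not need the exception if usual care were already exempt. That is not decisive, since the EDX arm would still need it.

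Two further inferences are tempting and not supported. One is that the trial cannot measure usual care at all; the checklist, baseline history and referrer interviews contradict this. The other is that objective 4 will be answered from the control group alone. The control-group percentages are only one planned summary. Co-interventions are recorded with no arm restriction, and resource-use data are to be analysed consistently with the clinical outcomes, so between-arm information will exist.

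The exclusions follow the LEAP trial and are not an error. They only limit how far the profile generalises.

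**Conclusion.** The point holds in a limited form. The Procedure section conflicts with the definition of usual care and with Table 3, and no sentence resolves the conflict. The leaflet wording and the caveat on community recruits leave the control condition less clear still. This is a contradiction in a stated rule, so it is not detail that an article would ordinarily leave to a fuller document.

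The consequence is that usual care and co-intervention observed after randomisation may be partly a product of the trial's request. That weakens objective 4 and makes the GROC effect harder to interpret for planning. Prescribed, past and current care remain measurable.

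The size cannot be calculated. It depends on how many of the planned 32 controls had non-drug care available, how many complied with the request, and how many were community recruits; the article gives none of these. The conclusion assumes that the request was put to both arms as written.

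**What to change.** 1. Reconcile the Procedure section, the Usual care section and Table 3 into one statement of what usual care participants are asked to do and may receive, including community recruits. Which rule applies is for the trial team. Because the article describes the trial as ongoing, also record what control participants have actually been told.
2. Describe the constituents of usual care mainly from the referrer checklist and the baseline treatment history of all randomised participants, with the control-group percentages as a supplement.
3. Tabulate co-interventions from the healthcare-use questionnaire in both arms and by recruitment stratum, with community recruits shown separately.
4. State with the results that the eligibility criteria exclude recent injection and recent physiotherapy, and that this limits how far the profile represents usual care.

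The cost is a wording change, any matching change to participant material, and a few extra descriptive tables. All the data are already planned. I do not suggest gathering treatment data on people screened out: that would be new data collection, and telephone screening comes before written consent.
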